### Randomisation

Patients will be randomised using an online platform (www.sealedenvelope.com) into either the intervention or control groups. Participants will be allocated in blocks of 10 with an allocation ratio of 1:1 to control (OTAGO HEP) and intervention (HOLOBalance) groups. Randomisation procedures will be run independently for each site and will be completed by a researcher external to the research study. No out of hours randomisation is required for this study.

Allocation will be concealed in consecutively numbered opaque envelopes which will be drawn up for each block and presented to the treating physiotherapist after the baseline assessment session has been completed. Allocation will not be revealed until after the baseline assessment has been completed, and once revealed will be entered onto the enrolment log.

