### Participants

One hundred and twenty independently living, community-dwelling older adults aged 65–80 who are at risk of falls will be recruited across three sites (London (UK), Freiberg (Germany), Athens (Greece)). Older adults who meet the following inclusion criteria for entry will be eligible to be enrolled.

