### Blinding

This is a single (assessor) blinded proof-of-concept study. As this study is comparing a technology intervention (HOLOBalance) versus standard care it is not possible to blind the participants or the treating clinicians to the intervention provided. The blinded outcome assessor will collect all of the outcome measures at baseline and follow-up with a single assessor being used at each site. Each assessor will be required to attend a training session prior to data collection to ensure consistency across sites. The outcome assessor will be asked to record any incidences of unblinding and detail how this occurred. Due to the nature of this study, we do not foresee circumstances where emergency unblinding of the outcome assessor is required.

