### Sample size

This proof-of-concept study will recruit 60 participants per group (ie, total sample size of 120). This will allow the researchers to gain preliminary data on the primary outcomes of safety, feasibility and acceptability of the HOLOBalance intervention. This will also provide sufficient data to explore trends for effectiveness and to allow for sample size estimates to be drawn up for a future trial.

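### A single block size of 10 at each site lets anyone who knows it and tracks earlier allocations foresee about 20 of 120 allocations with certainty, on average

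*Protocol article*

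**What the plan says.** Protocol article, Randomisation: "Participants will be allocated in blocks of 10 with an allocation ratio of 1:1 to control (OTAGO HEP) and intervention (HOLOBalance) groups". One block size is given and no variation is mentioned. In the same section: "Randomisation procedures will be run independently for each site and will be completed by a researcher external to the research study". So each site has its own list, produced by someone outside the study.

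On delivery, the section says: "Allocation will be concealed in consecutively numbered opaque envelopes which will be drawn up for each block and presented to the treating physiotherapist". The sentence goes on to place this after the baseline assessment session. The next sentence repeats that nothing is revealed before then, and that each revealed allocation is written on the enrolment log.

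Blinding: "it is not possible to blind the participants or the treating clinicians to the intervention provided". The outcome assessor is blinded.

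Recruitment gives telephone screening to a researcher, who books eligible people for baseline testing. Consent is taken on arrival at that session. Participants "will be recruited across three sites", with 120 in total; the split between sites is not stated. Under Primary outcomes, compliance and drop-out in each group are listed among the acceptability measures.

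**The concern.** In a 5:5 block of 10, once one arm has had its five places, every remaining place belongs to the other arm. With a constant, known block size and a separate list at each site, the end of every completed block can be worked out from the allocations already made. Numbered opaque envelopes do not prevent this, because the information comes from past reveals and not from the unopened envelope.

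At least some people at a site learn allocations as they occur. The treating physiotherapist receives them and cannot be blinded, and each one also goes on the enrolment log. If such knowledge reached the person deciding whom to book next, the arms could differ in who enters them. Compliance and drop-out by arm are primary outcomes here. They could plausibly depend on whether a participant suited to a head-mounted display or to an exercise booklet was booked at a given moment. The trial is also meant to inform a future trial, so a distorted drop-out figure would carry forward.

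**Working it through.** **Inputs.** Block size 10, ratio 1:1 and separate site lists (Randomisation); three sites (Participants); 120 participants, 60 per group (Sample size). *Assumption:* site totals are multiples of 10, for example 40/40/40, giving 120/10 = 12 complete blocks. The article states no predictability figure, so there is none to reproduce.

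**Certain allocations per block.** The allocation at position i is certain when the first k = i − 1 places already hold all five of one arm. The probability is 2·C(k,5)/C(10,5), with C(10,5) = 252:

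| Position | Probability certain |
|---|---|
| 1 to 5 | 0 |
| 6 | 2·1/252 = 0.008 |
| 7 | 2·6/252 = 0.048 |
| 8 | 2·21/252 = 0.167 |
| 9 | 2·56/252 = 0.444 |
| 10 | 2·126/252 = 1.000 |

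The sum is 420/252 = 1.667, which agrees with the closed form 2m/(m+1) = 10/6 for m = 5. Enumerating all 252 orders gives probabilities of 0.556, 0.278, 0.119, 0.040 and 0.008 for 1, 2, 3, 4 and 5 certain allocations in a block.

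**Whole trial.** 12 × 1.667 = 20.0 of 120, or 16.7%. The variance per block is 3.571 − 1.667² = 0.794, so the SD over 12 blocks is √(12 × 0.794) = 3.1. The central 95% is about 15 to 27 and the possible range is 12 to 60. The probability of exactly 20 is 0.13.

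**Unfinished blocks.**
- 45/40/35 has 11 complete blocks and two part-blocks of 5, which add nothing: 11 × 1.667 = 18.3.
- 48/36/36 has 10 complete blocks, one part-block of 8 and two of 6: 16.667 + 0.222 + 2 × 0.008 = 16.9.
- An uneven split in multiples of 10, such as 60/30/30, still gives 20.0.

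**Best guess.** Always guessing the arm with more places left gives an expected 5 + (2¹⁰/252 − 1)/2 = 6.53 correct per block. That is 65.3%, or 78.4 of 120, against 50% by chance.

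**Randomly varied block sizes.** Simulation with 40 per site and an observer who knows the set of sizes but not the current one:

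| Block sizes | Certain, of 120 | Best guess correct |
|---|---|---|
| 10 only | 20.0 | 65.3% |
| 6, 8, 10 | 2.1 | 65.8% |
| 4, 6, 8 | 2.7 | 67.6% |
| 4, 6, 8, 10 | 1.4 | 66.6% |

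An observer who does not know the set of sizes has almost no ground for certainty, so the count is then close to 0.

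**The case against.** The strongest reply is that the documents show no route from prediction to biased entry. Screening and booking belong to a researcher, consent and baseline come before the envelope, and the physiotherapist has no stated part in any of these. The list comes from someone outside the study, and the envelopes are opaque and numbered in sequence. The study is a proof of concept, declares no formal analysis plan and reports acceptability descriptively.

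Much of this stands. A reader might infer more than the documents support in five ways:

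- *That exactly 20 allocations are exposed.* Twenty is an expectation. It needs complete blocks and an observer who knows the size and every earlier allocation at the site. The article does not say that the physiotherapist is such a person, or who may read the enrolment log.
- *That staff will steer recruitment.* A leak to the screening researcher is possible, because the text neither separates that role from the treating team nor restricts the log. It is not shown.
- *That envelopes will be opened early or out of order.* Nothing says so. Custody and sealing are details that an article leaves to the full protocol.
- *That the assessor is compromised.* The figure of 20 does not apply to a blinded assessor, who would need several unblinded cases within one block to infer others. Incidents of unblinding are to be recorded.
- *That the trial is open-label.* Participants and clinicians are unblinded, but the assessor is blinded.

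What does not stand is the idea that the timing of the reveal settles the matter. It protects the allocation in hand, not those that can be deduced from earlier ones. The full protocol may say that the block size is withheld, but a single size is fixed and printed in the article. Low power and descriptive reporting are no reason to accept a predictability that costs almost nothing to remove.

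**Conclusion.** The point holds as a weakness in the randomisation scheme, not as evidence of selection bias. With a constant block of 10 per site, about 20 of 120 allocations (SD about 3) are expected to be certain in advance to someone who knows the size and tracks the site's earlier allocations. The figure is about 17 to 18 in the splits examined that leave blocks unfinished.

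It rests on three assumptions: whole blocks are filled, the block size is known, and earlier allocations are followed in full. Any effect on compliance or drop-out needs a fourth, that this knowledge reaches whoever screens or books. The documents neither establish nor rule that out.

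Varying the block size deals with certainty only. The best-guess rate is 65.3% now and 65.8% with blocks of 6, 8 and 10, so the change should not be presented as making allocations unguessable. It is still worth making, because the primary outcomes include comparisons by arm and the cost is small.

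**What to change.** Have the external researcher generate the site-stratified 1:1 lists with randomly varied block sizes, for example 6, 8 and 10, on the online platform already named. State in the protocol only that block sizes vary at random, and keep the sizes in a document that site staff cannot see. If enrolment has begun at a site, the change can start at its next block.

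The expected number of certain allocations then falls from about 20 to about 2 of 120 if the set of sizes becomes known, and to about 0 if it does not.

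The cost is a change of list settings and a sentence of amendment, with ethics approval where the protocol's own rule on amendments requires it. Sample size and stratification by site are unaffected. The statistical price is a possible small imbalance at a site that stops mid-block. The maximum is 5, as now, because the largest block is still 10. One difference remains: a site total that is a multiple of 10 is exactly balanced under the present scheme but need not be under the varied one.

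Releasing each allocation online after the baseline assessment, in place of envelopes, would remove the paper step. It is optional and the point does not depend on it.

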### Blinding

This is a single (assessor) blinded proof-of-concept study. As this study is comparing a technology intervention (HOLOBalance) versus standard care it is not possible to blind the participants or the treating clinicians to the intervention provided. The blinded outcome assessor will collect all of the outcome measures at baseline and follow-up with a single assessor being used at each site. Each assessor will be required to attend a training session prior to data collection to ensure consistency across sites. The outcome assessor will be asked to record any incidences of unblinding and detail how this occurred. Due to the nature of this study, we do not foresee circumstances where emergency unblinding of the outcome assessor is required.

### Interventions

Participants will be randomised to receive either the active intervention (HOLOBalance) or the control intervention (OTAGO HEP). Participants will be asked to perform their prescribed exercises daily, with each participant performing 40–60 min of rehabilitation per day (including rest breaks). Participants will receive home visits from their treating clinician at week 0, 3 and 6 to assess and progress their programme. All participants will have a telephone conversation with their treating clinician every week for the duration of their participation in the rehabilitation programme to discuss their exercise programme.

### Active intervention: the HOLOBalance system

HOLOBalance is an augmented reality balance training programme based on evidence-based MSR protocols.^49 50^ MSR requires individuals to regularly perform exercises which challenge the balance system (eg, closed eyes, stand on foam), optimise vestibular balance function and have been shown to improve balance control in healthy older adults^49 50^ and people with vestibular balance dysfunction.^51–54^

Participants will be required to wear a series of body worn sensors (pressure detecting insoles, intertial measurement unit (IMU) and a heart rate monitor, figure 2) when performing the exercises so that (1) the computer software can assess the participants performance and (2) the user can interact with the system. HOLOBalance will provide prescribed exercises and exergames presented into the person’s home environment by ahead mounted augmented reality display and log the user’s interactions with the system (eg, number of sessions completed). HOLOBalance will display a holographic virtual physiotherapist (figure 3A) to provide instructions and demonstrate prescribed exercises. The HOLOBalance programme will include exercises to maximise opportunities for balance improvement and include turning the head while looking at a target, standing on foam, and walking while turning the head (eg, of gameplay, please see figure 3B, C, and for table of basic exercises please see table 1). In addition, participants will be given auditory and cognitive exercises in supplement to their balance training programme. For further information on the HOLOBalance intervention, please visit www.holobalance.eu.

**Figure 2 F2:**
[figure not shown]
Diagram of the HOLOBalance system hardware.

**Figure 3 F3:**
[figure not shown]
Screenshots of (A) physiotherapist avatar, (B, C) representative gameplay from the HOLOBalance system.

**Table 1 T1:** The HOLOBalance intervention basic exercises and their progressions

Position	Description	Progressions	Progression activation
Seated	Head turns side to side (yaw rotation of 30°) while visually fixating on a static target placed at eye level in front of the participant	Increase speed of movements Visual target moves in opposite direction to head movement	Increase speed of head turns if patient reporting no symptoms If patient can perform three head turns (ie, left to right) in one second without provoking symptoms, move to next progression
				Seated	Had turns up and down (pitch rotation of 30°) while visually fixating on a static target placed at eye level in front of the participant	Increase speed of movements Visual target moves in opposite direction to head movement Look up to ceiling and down to floor without fixation	Increase speed of head turns if patient reporting no symptoms If patient can perform three head turns (ie, left to right) in one second without provoking symptoms, move to next progression
								Seated	Bend down to pick object up from the floor in front of you	Close the eyes Reach to pick up objects to the side	If patient can complete the full range of movement consistently in 2 s (or less) in eyes open condition, and no symptoms are provoked. Progress to eyes closed. When able to complete forward bends with eyes open and closed, progress to sideways bend.
Standing	Stand with feet hip width apart, looking straight ahead with eyes open	Bring feet closer together Close the eyes	If patient can maintain stability in the correct position for 1 min with eyes open without prompts, then ask patient to close eyes. If patient can maintain stability in the correct position with eyes closed, reduce base of support.								
				Standing	Stand on foam cushion with feet hip width apart and looking straight ahead with eyes open	Bring feet closer together Close the eyes	If patient can maintain stability in the correct position for 1 min with eyes open without prompts, then ask patient to close eyes. If patient can maintain stability in the correct position with eyes closed, reduce base of support.				
								Standing	Stand with feet hip width apart and bend over to pick up an object from the floor	Bring feet closer together Reach up as if to reach into a cupboard	When patient can safely complete full movement in less than 3 s, and this produces no symptoms, ask patient to increase speed. When patient can safely complete the full movement (without symptoms) in under 2 s, move on to the next exercise.
Standing	Step turn through 180° to face the opposite direction	Increase speed of movement	Once patient is able to perform the exercise safely and confidently at their baseline speed, ask them to increase their speed.								
				Walking	Walk forwards looking straight ahead	Increase walking speed	Once patient is able to perform the exercise safely and confidently at their baseline speed with no deviation, ask them to increase their gait speed.				
Walking	Walk forwards across the room looking between two targets placed at eye level, 1.5 m apart on the horizontal plane.	Increase walking speed Increase head turn speed Turn head fully to side as if crossing the street.	Once patient is able to perform the exercise safely and confidently at their baseline speed with no symptoms or deviation, ask them to increase their gait speed. Once patient is able to perform the exercise safely and confidently with no symptoms or deviation, ask them to increase their head turn speed Once patient is able to perform the exercise safely and confidently with no symptoms or deviation, ask them to increase amplitude of head turns				
				Walking	Walk across the room and nod your head to look up to the ceiling and down to the ground.	Increase walking speed Integrate diagonal head movements	Once patient is able to perform the exercise safely and confidently at their baseline speed with no symptoms or deviation, ask them to increase their gait speed. Once patient is able to perform the exercise safely and confidently with no symptoms or deviation, ask them to increase their head turn speed Once patient is able to perform the exercise safely and confidently with no symptoms or deviation, ask them to integrate diagonal head movements

### Control intervention: the OTAGO HEP

The OTAGO HEP booklet (available at https://www.livestronger.org.nz/assets/Uploads/acc1162-otago-exercise-manual.pdf) will be provided to all individuals in the control arm. Following the physiotherapy home assessment, participants will be provided with a list of exercises from the OTAGO booklet for them to complete every day. Participants will be required to log their exercises in an exercise diary for review by the treating clinician at the next home visit. Exercises will be progressed in line with the recommendations of the OTAGO HEP in combination with the treating clinician’s clinical judgement.

### Outcome measures

#### Primary outcomes

The primary outcomes will relate to the acceptability, safety and feasibility of providing the HOLOBalance intervention. Acceptability measures include; recruitment rate (percentage of eligible participants enrolled), compliance with interventions (percentage of prescribed sessions completed in HOLOBalance and control groups) and drop-out rates (number of drop-out in HOLOBalance and control groups). Exit interviews will be completed with participants that receive the HOLOBalance intervention to explore their experience of using the system, including perceived benefits, frustrations and recommendations. Interviews will be recorded, transcribed verbatim and subject to thematic analysis.

In the HOLOBalance group, adherence will automatically be monitored through the interaction with the system, and calculated as the number of prescribed balance exercises, auditory and cognitive training tasks completed per day, expressed as a percentage. In the control group, participants will be required to complete a daily exercise diary to report on their level of activity, whether they had completed their HEP session and whether they had performed their cognitive tasks. All participants will receive a weekly telephone call from the research physiotherapist to discuss any issues, their current progress and to remind them to complete their exercise diaries (if in the control group) which will be collected at their final outcome measure test session. The order of events for participants enrolled in this study is displayed in table 2.

**Table 2 T2:** Order of events for all participants enrolled in the HOLOBalance study

		Screening session	Baseline test session	Week 0	Daily	Weekly	Monthly	Week 3	Week 6	Follow-up test session	Week 9
Recruitment Procedures	Provide patient information sheet	X									
	Provide informed consent		X								
University-based data collection	Demographics		X								
	The MoCA		X							X	
	The RAPA		X							X	
	The WHODAS 2.0		X							X	
	The CANTAB		X							X	
	The ABC Scale		X							X	
	The FES-I		X							X	
	The EQ-5D		X							X	
	The EMA		X							X	
	The BREQ-3		X							X	
	Mini-BESTest		X							X	
	The FGA		X							X	
	Exit Interviews (HOLOBalance Group Only)										X
Usability Measures	The SUS								X		
	The UEQ			X				X	X		
Home-based interactions	Equipment installation and Removal (HOLOBalance Only)			X						X	
	Home visit from Physiotherapist			X				X	X		
	Telephone conversation with physiotherapist					X					
	Perform Home Exercise Programme				X						
	Submit falls diaries						X				

ABC, Activities Specific Balance Confidence Scale; BREQ-3, Behavioural Regulation in Exercise Questionnaire; EMA, Environmental Analysis of Mobility Scale; FES-I, Falls Efficacy Scale International; FGA, Functional Gait Assessment; mini-BESTest, Mini Balance Evaluation Systems Test; MoCA, Montreal Cognitive Assessment; RAPA, Rapid Assessment of Physical Activity; SUS, System Usability Scale; UEQ, User Experience Questionnaire; WHODAS 2.0, WHO Disability Assessment Schedule 2.

Safety of the HOLOBalance intervention will be assessed by recording and assessing all adverse/serious adverse events and device effects (and reporting these to appropriate agencies as required). These will be reported by participants to their treating clinician or by self-reporting on the HOLOBalance database. The feasibility of the study will be explored by collecting information on and analysing any deviations from protocol or problems with implementing the study protocol (eg, logistical problems).

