Balance rehabilitation typically consists of personalised sets of exercises, defined by a healthcare professional and is the only effective treatment for balance disorders, irrespective of a person’s age.^32–34^ Although exercises are typically brief and easy to perform, there is up to 50% lost to follow-up rate in older adults in these programmes, and while supervision significantly increases compliance and effectiveness,^35^ it is costly to provide. To this end, many falls prevention programmes provide exercise programmes completed either in group settings or independently at home.^36–41^ These programmes have been shown to be effective in reducing falls rates in older adults, reducing falls by 30%–40% (dependant on target population), however, they are limited in that they either do not provide exercises to address vestibular function or dual task training,^37–39^ or these are not introduced until very late in the programme.^40 41^ This is despite promising evidence suggesting that combined cognitive and functional training may provide improvements beyond single task training.^42–44^ Similarly, rehabilitation programmes which address vestibular dysfunction (ie, multisensory rehabilitation, MSR programmes) have been developed for older adults at risk for falls and have shown substantial additional reduction of falls risk to standard programmes.^45–47^ These programmes require customised, expert-led interventions to optimise recovery, however, there is limited availability of experts to provide these individualised interventions and these may hinder their translation into clinical practice.

The HOLOBalance telerehabilitation platform has been developed to address this lack of expert physiotherapists. HOLOBalance will provide a customised and interactive falls rehabilitation programme that incorporates: (1) functional balance training, (2) multisensory exercises to improve balance function and (3) cognitive-motor training, for older adults at risk for falls. HOLOBalance will use off-the-shelf technologies to allow clinicians to provide an individualised balance rehabilitation programme for older adults who will be able to participate in at a time of their choice and in their home environment (for system description please visit www.holobalance.eu). This study protocol outlines the multisite randomised controlled proof-of-concept study to explore safety, feasibility and acceptability of the HOLOBalance telerehabilitation system.

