## Methods and analysis

### Trial design

This study is an assessor-blinded, randomised proof-of-concept study to explore the acceptability and feasibility of providing a home-based balance telerehabilitation programme (HOLOBalance) to community-dwelling older adults at risk for falls. All participants will be enrolled in a 8-week home exercise programme (HEP) designed to improve balance function, and which adheres to the current guidance for strength and balance training.^30^ All participants will receive an exercise programme provided under the supervision of a physiotherapist with regular reviews by telephone (weekly) and home visits (week 0, 3 and 6). Exercises will be prescribed according to participant feedback and task performance as assessed by the treating physiotherapist.

This study will compare acceptability of the HOLOBalance telehealth programme (eg, compliance, drop-out rate) to an established HEP that is routinely used in community rehabilitation (the OTAGO HEP^23^) and will explore trends for effectiveness across a number of validated outcome measures to explore whether a future trial is warranted, and if so to provide data for a sample size estimate. For this proof-of-concept study, data will be collected at baseline (week 0) and at completion of the intervention (week 9). The flow of participants through the trial will be recorded in compliance with the Consolidated Standards of Reporting Trials statement (figure 1), and this protocol has been developed using the Standard Protocol Items: Recommendations for Interventional Trials reporting guidelines for clinical trials.^48^

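### Compliance is defined by session for both arms but calculated by task from the system log in HOLOBalance and by session from a self-report diary in OTAGO, so identical behaviour can score differently.

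*Protocol article*

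**What the plan says.** The Trial design section announces a between-arm comparison: "This study will compare acceptability of the HOLOBalance telehealth programme (eg, compliance, drop-out rate) to an established HEP". The Primary outcomes section gives the measure one definition for both arms: "compliance with interventions (percentage of prescribed sessions completed in HOLOBalance and control groups".

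The next paragraph of that section describes how adherence is obtained in each arm.

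- HOLOBalance: "In the HOLOBalance group, adherence will automatically be monitored through the interaction with the system, and calculated as the number of prescribed balance exercises"; the formula in full is "calculated as the number of prescribed balance exercises, auditory and cognitive training tasks completed per day, expressed as a percentage". The unit is the single exercise or task, and the source is a machine.
- OTAGO: "In the control group, participants will be required to complete a daily exercise diary to report on their level of activity", plus whether the home session and the cognitive tasks were done. The unit is the session, and the source is self-report.

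On timing, the control diaries are items "which will be collected at their final outcome measure test session". No section says how the compliance percentage treats days after drop-out, in either arm.

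Three other places bear on this. The section on the HOLOBalance system says that the system also logs a count of completed sessions. The section on the OTAGO programme has controls log their exercises, with the diary looked at by the clinician at the following home visit. The Interventions section schedules home visits at weeks 0, 3 and 6 and a telephone call every week, in both arms.

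**The concern.** A comparison of compliance is interpretable only if the same behaviour earns the same score in both arms. Followed literally, the text gives partial credit for a partly done day in HOLOBalance and a yes or no in OTAGO. A gap between arms could then reflect the scoring rule and not the participants.

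The collection point adds a second problem. The HOLOBalance log builds up day by day, whereas a control who leaves early has no stated point at which the diary is handed in. If those diaries are lost, the control figure describes completers, while the HOLOBalance figure may describe everyone randomised.

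Compliance feeds the judgement on whether a future trial is warranted. A misleading contrast could count for or against the system, and diary data not captured during follow-up cannot be recovered at analysis.

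**Working it through.** The protocol states no compliance rate, standard deviation, margin or significance level, so there is no figure of its own to reproduce. The check scores identical behaviour under each arm's rule. The only numerical input from the document is 60 participants per group (Sample size). All other values are assumptions.

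**Unit.** Let *a* be the share of days with a session and *s* the share of tasks done on those days.

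- Task rule (HOLOBalance): *a* × *s*.
- Session rule, lenient (any session counts as done): *a*. The gap is *a*(1 − *s*).
- Session rule, strict (done means all *K* tasks, treated as independent): *a* × *s*^*K*.

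| Assumed values | Task rule | Session rule | Higher score |
|---|---|---|---|
| a = 0.8, s = 0.8, lenient | 0.8 × 0.8 = 64% | 80% | control, by 16 points |
| a = 0.6, s = 0.9, lenient | 54% | 60% | control, by 6 points |
| a = 0.9, s = 0.6, lenient | 54% | 90% | control, by 36 points |
| a = 0.8, s = 0.9, strict, K = 5 | 72% | 0.8 × 0.9^5 = 47.2% | HOLOBalance, by 24.8 points |

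With *a* and *s* each between 0.6 and 0.9, the lenient reading gives gaps of 6 to 36 points towards control. The strict reading reverses the sign.

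**Drop-out.** Suppose that a fraction *d* leave halfway on average, that compliance while participating is *c* = 0.8, that every control drop-out's diary is lost, and that log days after drop-out count as zero. The log then reads (1 − *d*)*c* + 0.5*dc*, the diaries read *c*, and the gap is 0.5*dc*:

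- *d* = 10%: 76% against 80%, 4 points.
- *d* = 20%: 72% against 80%, 8 points.
- *d* = 30%: 68% against 80%, 12 points.
- *d* = 50%: 60% against 80%, 20 points. The Introduction mentions losses this high ("there is up to 50% lost to follow-up rate in older adults in these programmes"), but as background and not as a planning figure.

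**Both together.** With *a* = *s* = 0.8, the lenient reading and *d* = 20%, the log reads 0.8 × 64 + 0.2 × 0.5 × 64 = 57.6% against 80%, a gap of 22.4 points.

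**Set against the trial's precision.** The 95% half-width for a difference in means is 1.96 × SD × √(2/60), which is 7.2, 8.9 and 10.7 points for assumed SDs of 20, 25 and 30. A purely artefactual 16-point gap would reach two-sided p < 0.05 with probability 0.99, 0.94 and 0.83 at those SDs. For an 8-point gap the probabilities are 0.59, 0.42 and 0.31. No such test is planned; the figures only show that an artefact of this size would stand out from the noise.

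**After the fix.** With one session-level unit and one drop-out rule, identical behaviour gives a gap of 0 points from these two sources. Over- or under-reporting in the diary remains, and the document gives nothing from which to size it.

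**The case against.** The best defence is that the protocol already fixes one unit, the session, for both arms, and that the system logs sessions, so a like-for-like comparison is available. Controls also log exercises, so their record may be more than a tick. Diaries are seen at home visits, and weekly calls discuss progress, so a drop-out's data need not vanish. Some difference of source is unavoidable because controls have no device. Finally, this is a proof-of-concept study: the Abstract plans descriptive statistics for acceptability, the analysis section disclaims a formal plan, and no threshold rests on the contrast.

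Much of this stands. It limits the severity and shows that the remedy is close at hand. It does not remove the conflict: the only calculation given for HOLOBalance is at task level, directly after a session-level definition. The OTAGO section describes review of the diary, not collection or transcription.

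A reader might infer that the protocol treats drop-outs differently in each arm. It does not say so. It states no rule for either arm, and the asymmetry is a possible consequence of when diaries are collected. A reader might also infer that the bias favours control. The unit effect can run either way, depending on what a completed session means.

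**Conclusion.** The point holds as an internal inconsistency in a primary acceptability measure that is to be compared between arms. The session definition and the HOLOBalance calculation do not agree, and the two arms differ in both unit and source. With identical behaviour, the unit alone can produce a gap of 6 to 36 points under the lenient reading and a reversed gap under the strict one. Possible loss of drop-out diaries could add 4 to 20 points. These sizes rest on the assumed values above. The drop-out figures further require that all control drop-out diaries are lost and that later log days score zero, neither of which the document states. The supported conclusion is that the contrast cannot be interpreted as written, not that it is biased in a known direction or by a known amount. The HOLOBalance log remains a sound measure within its own arm.

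A related conflict affects the task denominator. Controls are asked to report cognitive tasks, but the OTAGO section gives them only exercises from the booklet, and the auditory and cognitive exercises are described only for HOLOBalance. These passages must be reconciled.

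**What to change.** For the between-arm comparison, use one definition: prescribed sessions completed divided by all prescribed sessions over the 8 weeks, for every randomised participant. State what counts as a completed session, in the same terms for both arms, and apply one stated rule to days after drop-out in both arms.

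Take the numerator from the session count that the system already logs and from the session item in the control diary. Transcribe the diary to the case report form at the weekly calls and at the week 3 and week 6 visits, so that data up to drop-out are kept. Retain the task-level percentage as a HOLOBalance-only measure. Report the remaining difference between log and self-report as a limitation.

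Reconcile the HOLOBalance, OTAGO and Primary outcomes sections on whether controls have cognitive tasks.

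The cost is some protocol wording and a little extra data entry at contacts already scheduled. Adding a daily diary in the HOLOBalance arm would equalise the source, but it adds burden and could itself alter adherence. It is a debatable trade-off and is not needed here.
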